#### Follow-up visits

Follow-up visits at 12 and 24 months will be identical to the baseline visit. Follow-up visits at 6 and 18 months will be the same with the baseline visit, with the only exception that the cognitive function test and mtDNA-CN will not be performed. This is due to the fact that we estimate that more than 6-month time would be required to detect any potential changes in these parameters [34].

Participants will be provided with a copy of the food diary they had completed prior to the baseline visit and will be asked to replicate their diet, 4 days before each follow-up visit, to avoid any potential effect of changed nutritional habits on the measured blood markers. They will also be reminded to avoid any strenuous physical activity during this time. At every follow-up visit, we will collect any WURSS-21 and GISS-16 questionnaires completed during the previous 6 months, from participants that experienced respiratory tract symptoms or gastrointestinal discomfort. We will also collect any leftover capsules from the previous 6 months, to monitor intervention compliance. Participants will be contacted via telephone in between visits with a cadence of 3 months, by a member of the research team, to keep them motivated and ensure maximum retention to the trial.

Figure 1 summarises participants’ recruitment and follow-up plan, according to the Consolidated Standards of Reporting Trials (CONSORT) 2010 statement. Figure 2, provides an overview of the schedule of interventions and all study procedures performed at each study visit, according to the Standard Protocol Items: Recommendations for Interventional Trials (SPIRIT) guidelines [35].

**Fig. 1 Fig1:**
[figure not shown]
CONSORT flow diagram

**Fig. 2 Fig2:**
[figure not shown]
SPIRIT figure showing the schedule of interventions and assessments

#### Adverse events assessment and reporting

An adverse events reporting system is in place for this study. Any adverse events will be collected after a participant has provided consent and enrolled in the study. The study physician will continuously assess participants’ medical history throughout the study and will refer participants to a specialist expert, should this be necessary. In case the health status of a participant changes during the study or in case of any other concern, the study physician will assess the continuation or withdrawal of the participant from the study.

#### Ancillary care

Participants enrolled in this study are covered by liability insurance provided by the supplementation company and is valid for the entire duration of the study.

### Analytical assessments and measurement tools

#### Height, weight, BMI and blood pressure

Height will be measured to the nearest 0.1 cm using a stadiometer (Seca 217) and weight to the nearest 0.1 kg using calibrated mass scales (Seca robusta 813). BMI will be calculated by dividing weight in kg by the square of height in m. Two blood pressure readings on each arm, using an automated blood pressure monitor (Boso medicus x), will be recorded while the participant is in a seated position.

#### Blood markers

A total of 47 ml from each participant will be collected by venepuncture by the study physician at each visit for the analysis of blood biomarkers of cardiovascular health, low-grade inflammation, selected indicators of ageing, vitamins, carotenoids and fatty acids. Aggregation and thrombelastometry parameters will be immediately measured in fresh whole blood. 1mL of whole blood will be stored at −80°C for future analysis of mtDNA. Blood samples for the clinical chemistry analyses will be transported immediately after collection to another collaborating laboratory for analysis. Remaining blood will be centrifuged at 3000 rpm for 10 min to get the plasma. The supernatant will be frozen at −80°C and kept at the study site for further analysis.

Blood lipids including total cholesterol, LDL, HDL, triglycerides and ApoA1, as well as homocysteine, hsCRP and vitamin D will be measured by the standard equipment Architect ci8200 (Abbott Diagnostics, IL, USA). Glucose and HbA1c will be measured photometrically using the Alinity system (Abbott, IL, USA) and insulin by the fully automated chemiluminescence analyser LIAISON® XL (DiaSorin, Italy). HOMA-IR will be calculated from glucose and insulin. oxLDL will be analysed by solid phase two-site enzyme immunoassay (Mercodia Inc, Sweden).

Whole blood aggregation parameters, including amplitude, slope and lag time, will be assessed by a Chrono-Log Whole Blood Aggregometer, model 590 from Probe & Go (Endingen, Germany), which is based on the impedance method.

Thrombelastometry (TEM) parameters including coagulation time (CT), clot formation time (CFT), maximum clot firmness (MCF) and alpha angle will be assessed by the TEM coagulation analyser ROTEM®05 (Matel Medizintechnik, Austria). Prothrombin time (PT) and partial thromboplastin time (PTT) will be determined using the apparatus ACL Top LTS 300 (Werfen GmbH, Germany).

Malondialdehyde (MDA) will be determined by high-performance liquid chromatography (HPLC) and carbonyl proteins (CP) by a carbonyl protein enzyme-linked immunosorbent assay (ELISA) kit (Immundiagnostik AG, Germany). Redox state of albumin will be determined by separating albumin into three fractions; human mercaptalbumin (HMA), human non-mercaptalbumin1 (HNA1) and human non-mercaptalbumin2 (HNA2). HMA, HNA1 and HNA2 will be determined by means of HPLC.

The plasma levels of IL-5, IL-8, TNF-α, sTNFR1, sTNFR2, CCL2, CCL5, IL-1β and osteoprotegerin will be determined using a customised 9-Plex immunoassay (Human magnetic Luminex assay, R&D Systems, US).

Plasma levels of dp-ucMGP will be measured with the IDS-iSYS InaKtif MGP (dp-ucMGP) assay on an IDS-iSYS Multi-Discipline Automated System (ids Immunodiagnostic Systems, UK), according to the manufacturer’s instructions. Undercarboxylated osteocalcin will be determined by a sandwich ELISA kit (Novus Biologicals, Bio-Techne).

Plasma levels of BDNF and NGF will be determined using a customised multiplex immunoassay, which allows the simultaneous quantitation of multiple cytokines in a single sample (Human magnetic Luminex assay; R&D Systems).

For the measurement of mitochondrial DNA copy number (mtDNA-CN), DNA will initially be isolated from anticoagulated whole blood on a MagNA Pure instrument (Roche, Vienna, Austria). mtDNA-CN will subsequently be measured by multiplexed real-time quantitative polymerase chain reaction (qPCR) utilising ABI TaqMan chemistry (Applied Biosystems).

Tocopherols, retinol and β-carotene will be measured with ClinRep® kit (Recipe Chemicals + Instruments GmbH, Germany) by means of HPLC. Alpha-carotene, lutein, zeaxanthin, β-cryptoxanthin and lycopene will be determined and quantified via external standard curves. Vitamins C, K1 and K2 will also be determined by HPLC.

Total fatty acids (FAs), free and esterified, will be measured by the gas chromatograph–electron impact–mass spectrometer (GC-EI/MS), Agilent GC-MSD 5977 (Agilent, USA). Human plasma will be diluted in methyl-tert-butylether (MTBE) and methanol. Each sample will be spiked with a 400 nmol FA 17:0 as internal standard. The mass spectrometer will run in electron impact mode, and FAs are detected in full scan of m/z 80–400. Peak areas for FAs will be calculated by MassHunter and related to FA 17:0 internal standard peak areas. Quantities for FAs will be calculated by a one-point calibration (target FA vs FA 17:0).

#### Cognitive function

Cognitive function will be assessed via the Cognitive Functions Dementia index (CFD index), proposed by Jahn and Heßler [36]. Cognitive performance is estimated via the following 4 dimensions: (1) attention (alertness, shared attention, processing speed), (2) verbal long-term memory, (3) executive functions (spatial working memory, cognitive flexibility) and (4) expressive language (word fluency, object designation).

Participants will complete a series of tasks involving the above dimensions electronically and results of the individual tests, and a total score will be automatically calculated. Results are fed back by a percentage ranking via comparison to standard sample. Scores falling in a percentile rank between 16 and 100 are considered clinically normal, scores between percentile ranks 4 and 15 denote mild cognitive impairment, and those between percentile 0 and 3 denote severe cognitive impairment.

#### Quality of life

Physical and mental health-related quality of life will be assessed via completion of the Short Form Health Survey (SF-36). It consists of 36 questions assessing 8 domains, namely (1) physical functioning, (2) role limitations due to physical health, (3) role limitations due to emotional problems, (4) energy/fatigue, (5) emotional well-being, (6) social functioning, (7) pain and 8) general health. All items are scored on a scale from 0 to 100, with higher scores representing a better health state [37].

#### Stress profile

Participants’ stress profile will be assessed via completion of the Perceived Stress Scale (PSS-10) questionnaire developed by Cohen et al. [38]. It consists of 10 questions, and for each question, individuals are asked to select how often they felt a certain way in the last month, ranging from never to very often. Individual scores can range from 0 to 40 with higher scores indicating higher perceived stress. Depending on the score, individuals are classified as experiencing little, moderate or high levels of stress.

#### Physical activity assessment

To assess participants’ physical activity, the International Physical Activity Questionnaire—Short Form (IPAQ-SF) will be used. A previous study [39] has shown acceptable reliability (Spearman coefficient *r* = 0.54) for total activities, in German-speaking, middle-aged people, which is a similar cohort to ours. The IPAQ-SF comprises of 7 questions which ask completers about the frequency (days/ week) and duration (hours or minutes/ day) they spent being physically active in the last 7 days. The types of activities included are walking, moderate-intensity and vigorous-intensity activities. The calculations are based on the metabolic equivalents (MET) principle and the questionnaire suggests three levels of physical activity: low, moderate and high [40].

#### Upper respiratory tract symptoms

For an exploratory assessment of the incidence, duration and severity of upper respiratory tract symptoms, the Wisconsin Upper Respiratory tract Symptoms Survey (WURSS-21) will be used. The WURSS-21 questionnaire contains 21 questions and is an evaluative illness-specific quality of life instrument, designed to assess the negative impact of acute upper respiratory tract infection, presumed viral (the common cold) [41, 42].

#### Gastrointestinal symptoms

For an exploratory assessment of the incidence, duration and severity of gastrointestinal symptoms, the Gastro-Intestinal Symptoms Survey (GISS-16) will be used. The GISS-16 questionnaire was developed based on an adaptation of the WURSS-21. For the needs of this study, the survey includes 16 questions.

#### Nutritional assessment

Participants’ nutrition will be assessed via analysis of the food diaries recorded prior to the baseline visit, using the nutritional assessment program nut.s science database (version 1.32.81, Dato Denkwerkzeuge, Vienna, Austria). All participants will be provided with a copy of their nutritional output.

#### Data collection, storage and management

All team members will receive appropriate training on all measurements taken prior to the start of the trial. Collected data will be anonymised and linked to unique ID numbers, ensuring that participants’ confidentiality is maintained. Records that contain names or other personal identifiers will be stored separately from study records identified by ID number. Data collected in paper copies will be safely stored in locked cabinets. All study data will be recorded electronically on a server platform, where only authorised team members will have access to. In order to ensure accuracy of data, we will perform random data checks and range checks.

#### Sample size

The sample size calculation was performed according to omega-3 index changes as a key biomarker of cardiovascular health and TNF-α changes as a key biomarker of low-grade inflammation, following supplementation. Assuming a two-tailed t-test using 5% significance level (two-sided), a sample size of 18 and 19 subjects per group was determined to have 80% power to detect a 30% increase on omega-3 index [32] and a minimum decrease of 0.4 ng/L on TNF-α [43], respectively. Allowing for a dropout rate of 30% over 24 months, we aim to recruit 112 participants in total (*n* = 28 control group; *n* = 28 FVB group; *n* = 28 Omega group; *n* = 28 FVBO group).

### Statistical analysis

Statistical analysis will be performed using the Statistical Package for the Social Sciences (SPSS) software (version 24.0, IBM Corporation, Chicago, IL) by an independent statistician, blinded to participants’ group allocation. Metric data will be presented as mean ± SD. Statistical significance is set at *P* < 0.05. Normally distributed data fulfilling variance homogeneity will be analysed by one- and two-factorial (either ‘time’ or ‘time x treatment’) repeated measures analysis of variance (ANOVA) and covariance within each group and between all groups. Normal distribution will be determined by the Shapiro–Wilk test and homogeneity of variance by the Levene test. For post hoc analyses we will use the Bonferroni(–Holm) correction and/or Tukey’s post hoc test.

If it is not possible to use metric data, nonparametric tests will be used like the Friedman test (within group) and the Kruskal–Wallis test (between groups). If differences between groups reach significance, the Bonferroni–Holm method will be used to determine the localisation of the differences.

In addition, we will conduct comprehensive correlation analyses to compute relations within each outcome category and between the different outcome categories.

Statistical analyses will include data from all participants with an adherence to the study protocol (intervention compliance) of > 80%.

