**Methods:**

In this randomised, controlled, open-labelled, parallel-grouped clinical trial, 112 participants will be allocated to one of four arms (*n* = 28 on each arm): an encapsulated juice powder concentrate, a plant-based omega fatty acid supplement, both or a control group. We aim to investigate whether long-term separate or combined ingestion of the two can affect biomarkers of cardiovascular health, low-grade inflammation and indicators of ageing, including cognitive function, in middle-aged and elderly people. We will additionally explore the effect of the different supplementations on plasma levels of vitamins, carotenoids and fatty acids. Intervention will last 2 years and participants will be assessed at baseline and at follow-up visits at 6, 12, 18 and 24 months.

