### Study outcomes

The co-primary outcomes will be changes on markers of cardiovascular health and low-grade inflammation following 24 months of supplementation. Secondary outcomes include changes on selected indicators of ageing, upper respiratory tract symptoms and quality of life. Finally, tertiary outcomes include plasma concentration changes of vitamins, carotenoids and fatty acids.

A detailed summary of all parameters to be assessed is given in Table 2.

**Table 2 Tab2:** Detailed summary of primary, secondary and tertiary outcome parameters

Primary outcomes	Low-grade inflammation
Cardiovascular health	
Total cholesterol, LDL, HDL, ApoA1, TG, oxLDL, homocysteine, omega-3 Index, platelet aggregation, TEM, coagulation (PT, PTT), glucose, insulin, HOMA-IR, HbA1c, MDA, CP, redox state of albumin	TNF-α, sTNFR1 and sTNFR2, CCL5, IL-1β, hsCRP, CCL2, OPG, IL-5, IL-8

Secondary outcomes	Upper respiratory tract symptoms	Quality of life
Selected indicators of ageing		
uc-osteocalcin, dp-ucMGP, mtDNA-CN, BDNF, NGF, CFD index	WURSS-21	SF-36

Tertiary outcomes	Fatty acids
Vitamins and carotenoids	
Retinol, vitamins C, D, E (α-tocopherol and γ- tocopherol), K1, K2 (MK-7), α-carotene, β-carotene, lutein, zeaxanthin, lycopene, β-cryptoxanthin	DHA, DPA, EPA, AA, ALA, linoleic acid, oleic acid, palmitoleic acid, stearic acid

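### The repeated-measures ANOVA over five visits does not test the 24-month change named as primary, and as named it needs complete data from every participant

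*Protocol article*

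**What the plan says.** Under Study outcomes, the co-primary outcomes are "changes on markers of cardiovascular health and low-grade inflammation following 24 months of supplementation". The abstract's Methods paragraph says that "participants will be assessed at baseline and at follow-up visits at 6, 12, 18 and 24 months". Under Follow-up visits, the 6- and 18-month visits match baseline "with the only exception that the cognitive function test and mtDNA-CN will not be performed". Both of those measures are secondary, so every primary blood marker has five planned values.

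Under Statistical analysis, normally distributed markers are analysed with time, or time x treatment, as factors in "repeated measures analysis of variance (ANOVA) and covariance within each group and between all groups", using "Statistical Package for the Social Sciences (SPSS) software (version 24.0"). Bonferroni(-Holm) and/or Tukey post hoc tests follow. The section names no comparison at 24 months, no mixed model and no imputation. It also says: "Statistical analyses will include data from all participants with an adherence to the study protocol (intervention compliance) of > 80"%.

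Under Sample size, the calculation is a two-sided t-test at 5% with 80% power, giving 18 per group (omega-3 index) and 19 per group (TNF-α). "Allowing for a dropout rate of 30% over 24 months", the total becomes 112, or 28 per arm.

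**The concern.** The three sections point at different things. The outcome is a change at one time point and the sample size rests on a t-test, but the named test is an interaction across all visits. A significant interaction could come from a transient difference at 6 or 12 months that has gone by 24 months, and could then be reported as a positive primary result. A non-significant one does not answer the 24-month question either.

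The second part concerns incomplete data. Classical repeated-measures ANOVA works on participants with a value at every visit; adding a covariate does not change that, and the Friedman fallback has the same requirement. Someone who attends at 24 months but missed the 12-month visit is lost. So are the 6-18 month values of everyone who drops out later. In a two-year open-label trial whose own Discussion names commitment to visits as a weakness, such gaps are to be expected.

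**Working it through.** **1. The plan's own figure.** 19 / 0.70 = 27.1, rounded up to 28 per arm; 28 x 4 = 112, as stated. Expected completers are 28 x 0.70 = 19.6 per arm against 19 required, a margin of 0.6.

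**2. Implied effect size.** No SD is given. A two-sample, two-sided t-test at 5% with 80% power and 19 per group implies a standardised difference of d = 0.934. For TNF-α that means an SD of 0.4 / 0.934 = 0.43 ng/L. This d is used below.

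**3. Missed interim visits.** If a fraction m of those reaching 24 months misses each of the 6-, 12- and 18-month visits independently, complete rows per arm number 19.6 x (1 - m)^3. The protocol gives no m, so a range is shown.

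| Assumed m | Complete rows per arm | t-test power at d = 0.934 |
|---|---|---|
| 0 | 19.6 | 81% |
| 2% | 19.6 x 0.941 = 18.4 | 79% |
| 5% | 19.6 x 0.857 = 16.8 | 75% |
| 10% | 19.6 x 0.729 = 14.3 | 67% |

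These losses come before the compliance rule and on top of the 30% allowance.

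**4. What the interaction tests.** Degrees of freedom: (4 - 1) x (5 - 1) = 12. The null hypothesis is that all four profiles are parallel over all five visits. A difference in 24-month change is only one way of violating it.

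**5. Simulation.** Four arms, five visits, 19 per arm with complete data, compound-symmetric correlation 0.6 (assumed), effect d = 0.934 on the change-score scale, 4000 runs per scenario.

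| Scenario | Interaction, 12 df | 24-month change t-test, one arm vs control | Baseline-adjusted 24-month contrast, one arm vs control | Same adjusted contrast at 0.05/3 |
|---|---|---|---|---|
| One arm, effect at 6 and 12 months only | 97% | 5% | 5% | 2% |
| One arm, effect at 6 months only | 85% | 5% | 5% | 2% |
| One arm, linear rise to 24 months | 72% | 81% | 89% | 77% |

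Separate runs of the linear scenario gave 72-74% for the interaction, 88-89% for the adjusted contrast, and 76-78% for that contrast at 0.05/3.

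**6. Splitting the power gap (linear scenario).** Interaction to unadjusted 24-month contrast: 81 - 72 = 9 points. Adding baseline adjustment: 89 - 81 = 8 points. About half of the gap is therefore due to baseline adjustment. At 0.05/3 the unadjusted change contrast falls to about 65-67%, below the interaction.

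**7. A case favouring the interaction.** If both omega-containing arms plateau from 6 months, the interaction has 95% power, against 93-94% for a one-way test of the 24-month change across the four arms.

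**The case against.** Several points on the other side stand.

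- Neither listwise deletion nor a single model holding all five visits is stated. Both follow from the named method and the visit schedule, and a separate analysis plan could add imputation or contrasts.
- The 30% dropout is already budgeted, so it would be wrong to count all dropouts as unplanned loss of power. Only participants who reach 24 months with a missed interim visit are extra, and the article plans telephone contact every three months to limit attrition.
- A reader might infer that the ANOVA is unbiased only if dropout is completely random, and so that bias enters every primary comparison. The documents do not support that. Dropout that depends on arm alone does not bias differences in mean change. Bias needs dropout related to the marker's course, and nothing in the article speaks to that.
- A reader might also take the gap of about 15 points between 73% and 88% as the cost of the wrong test. That sets an omnibus test against a single uncorrected contrast. About half of the gap is baseline adjustment, which the article's reference to covariance does not rule out, and most of it disappears after correction for three comparisons.
- Corrected post hoc tests could locate a difference in time, and the Discussion calls the study explorative.

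The last point does not remove the mismatch. No 24-month comparison is named among the post hoc tests, and the article still declares co-primary outcomes and a powered sample size.

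**Conclusion.** The point holds, and it should be corrected before analysis. The firm part is the target: the named test can be significant with no difference in the primary outcome, in about 97% of simulated runs for an effect confined to 6-12 months in one arm. That figure rests on the assumed correlation of 0.6 and an effect of the planned size.

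The complete-data requirement is a real but smaller cost: power of about 79-75% if 2-5% miss each interim visit, with interim data from dropouts discarded and bias possible if dropout relates to the marker. The missed-visit rates are assumptions.

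The case for change does not rest on a large gain in power. Under a gradual effect it is about 73% against 76-78% after multiplicity correction, and the interaction is not weaker in every scenario.

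**What to change.** Replace the repeated-measures ANOVA for the primary markers with a linear mixed model: REML, unstructured covariance, outcome values at 6, 12, 18 and 24 months, and fixed effects for arm, visit, arm x visit and baseline, fitted to all available post-baseline values. State that the primary test is each supplement arm versus control at 24 months with multiplicity correction over the three comparisons, and that other visits are supportive.

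State the analysis set in the same place: all randomised participants with any post-baseline value for the primary analysis, with the set above 80% compliance kept as supportive. This is a separate and deliberate change, because the mixed model alone does not bring back anyone whom the compliance rule removes. Nor does the model cure dropout that depends on unobserved values.

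The cost is revised analysis text and slightly more analysis and reporting. Visits, assays and sample size are unchanged, and the named SPSS package can fit the model.

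### Preliminary Shapiro–Wilk and Levene tests decide, marker by marker, whether a co-primary outcome gets a time-by-treatment analysis or rank tests that have no such term and take no baseline covariate

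*Protocol article*

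**What the plan says.** Under Study outcomes, the protocol article defines the primary endpoint as a change: "The co-primary outcomes will be changes on markers of cardiovascular health and low-grade inflammation following 24 months of supplementation". The inflammation list in Table 2 of that section is "TNF-α, sTNFR1 and sTNFR2, CCL5, IL-1β, hsCRP, CCL2, OPG, IL-5, IL-8". Assessments are at five visits: "participants will be assessed at baseline and at follow-up visits at 6, 12, 18 and 24 months".

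Under Statistical analysis, the main route is conditional: "Normally distributed data fulfilling variance homogeneity will be analysed by one- and two-factorial (either ‘time’ or ‘time x treatment’) repeated measures analysis of variance". The same sentence adds a covariance analysis, both inside each arm and across the arms. The condition is settled by tests on the trial data: "Normal distribution will be determined by the Shapiro–Wilk test and homogeneity of variance by the Levene test". The alternative opens with "If it is not possible to use metric data" and continues "nonparametric tests will be used like the Friedman test (within group) and the Kruskal–Wallis test (between groups". If groups then differ, Bonferroni–Holm locates the differences.

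The section names no transformation, no covariate for the covariance analysis, no rank-based model with a covariate, and no variable on which Kruskal–Wallis is to be run.

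**The concern.** The two routes do not answer the same question. The time-by-treatment term in the parametric route asks whether the course of a marker differs between arms. Friedman asks whether a marker moves over time inside one arm, with no reference to control. Kruskal–Wallis asks whether arms differ on one variable, with no time factor and no adjustment. A co-primary marker that passes the preliminary tests gets the first question, and one that fails gets the other two.

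Three things are at stake. The analysis of a co-primary outcome is not known until the data have been tested. Results are not comparable across the markers of one co-primary family. And the endpoint is a 24-month change, while the fallback as written need not compare change between arms at all.

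**Working it through.** **1. The plan's own figure.** The Sample size section gives 19 per group for TNF-α and 30% dropout: 19/0.7 = 27.1, rounded up to 28, and 4 × 28 = 112. This matches the protocol. The 19 itself cannot be re-derived because no SD is given. For a two-sample t-test at two-sided 5% and 80% power, 19 per group implies a standardised difference d = 0.934, that is, a TNF-α SD of 0.4/0.934 ≈ 0.43 ng/L. I use 19 per arm and d = 0.934 below.

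**2. What each named test contains.**

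| Test | Compares arms | Time term | Treatment-by-time | Baseline covariate |
|---|---|---|---|---|
| Repeated-measures ANOVA/covariance | yes | yes | yes | possible; none named |
| Friedman | no | yes, within one arm | no | no |
| Kruskal–Wallis | yes | no | no* | no |

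*Run on 24-month change, it would be a two-time-point form of treatment-by-time. The section does not say this.

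**3. How often the gate could send a marker to the fallback.** The lognormal shape is an assumption. By simulation, with 19 in one arm at one visit, Shapiro–Wilk rejects in about 62% of samples at log-SD 0.6 and 81% at log-SD 0.8. At log-SD 0.3 and 0.5 it is about 22–26% and 49–50%. For truly normal data the answer depends on how many tests are run and on whether a single failure is enough. One visit in four arms gives 1 − 0.95⁴ = 18.5%. Four arms by five visits gives 1 − 0.95²⁰ = 64%. The protocol states neither rule.

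**4. Power of each route.** Assumptions: two arms of 19, lognormal marker, log-SD 0.8, equal correlation ρ between all visits, and an effect constant from 6 months. The log-scale effect is 0.934 × 0.8 × √(1 − ρ²), set so that a t-test on the baseline-adjusted scale has about 80% power: 0.647, 0.598, 0.534 and 0.448 for ρ = 0.5, 0.6, 0.7 and 0.8.

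| Analysis | ρ = 0.5 | 0.6 | 0.7 | 0.8 |
|---|---|---|---|---|
| Log-scale ANCOVA of 24-month value | 79% | 78% | 79% | 79% |
| Kruskal–Wallis, 24-month value | 67% | 56% | 49% | 35% |
| Kruskal–Wallis, raw change | 48% | 50% | 55% | 56% |
| Kruskal–Wallis, relative change | 65% | 68% | 71% | 73% |
| Planned interaction, untransformed | 37% | 41% | 43% | 45% |

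With a Greenhouse–Geisser correction, the last row falls to 29–37%. Repeated simulation moves single entries by a few points, so over all runs the ranges are 35–67% (24-month value), 47–58% (raw change), 64–73% (relative change) and 29–45% (interaction).

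**5. Sensitivity to the set-up.** In step 4 the effect shrinks as ρ rises, which drives the fall in the second row. Now hold the effect fixed: four arms of 19, log-SD 0.5, two arms shifted by −0.35 on the log scale. For ρ = 0.3/0.5/0.7/0.8, Kruskal–Wallis on 24-month values has 69/66/68/69%, on raw change 42/55/80/93%, and log-scale ANCOVA 75/82/95/99%. Type I error is about 5% for all three. The gaps change, but ANCOVA is ahead at every correlation.

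**The case against.** **The fallback can compare change with control.** Study outcomes and Sample size both speak of changes, so Kruskal–Wallis on the 24-month change is compatible with the document. This stands. A reader might infer that skewed markers would never get a between-arm comparison of change; the text does not support that. What remains is that the section leaves the variable open, and that even on change the test takes no baseline covariate and is less efficient than the adjusted model.

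**The power loss is measured against a model that the protocol never planned.** This also stands. A reader might infer that diversion to rank tests costs power compared with the planned analysis. On the assumed skewed data, the planned untransformed interaction does worse than Kruskal–Wallis on change.

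**The gate is under-described.** The protocol does not say whether raw values, changes or residuals are tested, over how many cells, or whether one failure is enough. So the claim that it tests raw outcome cells, and the 64% failure rate for a normal marker, are possibilities and not findings. The opening words of the fallback are loose too. Gate failure is the natural reading, because no other route is given for markers that fail.

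**Skewness is not documented.** No distribution is reported for TNF-α or any other marker. That TNF-α would be diverted cannot be concluded.

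**Such detail can sit in an analysis plan, and the study is described as explorative.** Leaving out a transformation or a covariate would not be a finding. But the protocol goes further: it fixes a data-dependent rule for outcomes that it calls co-primary, and it sizes the trial on two of them.

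**Conclusion.** The point holds in this form: tests on the trial data select the analysis of each co-primary marker, and the rank tests named for markers that fail contain no treatment-by-time term and take no baseline covariate. That follows from the text alone.

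The size is illustrative and rests on assumed lognormal markers, log-SD 0.6–0.8 for the gate and 0.8 for power, 19 per arm, and baseline correlation 0.5–0.8. Under those assumptions the gate rejects in about 62–81% of single arms. Both routes in the protocol fall short of the roughly 79% power of log-scale ANCOVA: the rank tests at 35–73%, depending on the variable analysed, and the untransformed interaction at 29–45%. The case is therefore for replacing both routes. Removing the diversion while keeping the untransformed interaction would not recover the power.

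**What to change.** Delete the Shapiro–Wilk/Levene gate. Before analysis and blind to allocation, fix one baseline-adjusted between-arm model of the 24-month value for every co-primary marker. Name in advance the concentration markers expected to be right-skewed, analyse them on the log scale, and report ratios of geometric means. Check residuals from the fitted model. Use a rank-based ANCOVA, which keeps both treatment and baseline, as the sensitivity analysis in place of Friedman and Kruskal–Wallis.

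The cost is wording only: no further participants, visits or assays. The one downside is that logged markers are read as ratios rather than differences.
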